#### Strategies to improve adherence to interventions {11c}

Rater for the screening, baseline, post-treatment, and follow-up is trained in the used tests, interviews, and computer programs: Global Assessment of Functioning (GAF), Structured Clinical Interview for DSM-5 for clinical diseases (SCID-5-CV), Autism Diagnostic Observation Scale, Version 2 (ADOS-2), Intelligence test (MWT-B and CFT 20-R), and Multifaceted Empathy Test (MET).

Therapists are trained in the application of Freiburg Asperger-Specific Therapy (FASTER) and in the administration and supervision of the Social Cognition Training Tool (SCOTT&EVA).

Video recordings from the trainings together with all manualized materials will be provided on a login-protected internet platform for raters and therapists. Thus, each study center can refresh their trainings or train new study members.

Once a month, there will be a telephone supervision for potentially emerging rating and therapy questions. Additionally, for all FASTER group therapy sessions, therapists are videotaped. These recordings will be used for supervision and adherence checks. Video cameras are placed in such a way that the study participants are not visible, only their voice is recorded. For that reason, written consent for the recording of study participants audio will be obtained.

#### Relevant concomitant care permitted or prohibited during the trial {11d}

In case of acute problems or comorbid disorders that have to be treated, all participants irrespective of their group are allowed to make use of outpatient visits, such as family doctor visits, outpatient psychiatric visits for comorbid mental disorders, doses adaptation of medication, and psychotherapy for comorbid disorders outside the study center. However, patients are not allowed to participate in specific therapy targeting the core problems of ASD during the whole trial phase and are not allowed to have received specific ASD therapy (individual and/or group therapy) for the core problems of ASD up until 6 months before inclusion into the study. It is also not permitted to change the active substance of psychotropic drugs during the study period. Participants may receive an overall maximum of up to 120 min of individual, non-ASD-specific consultation with study personnel within their period of participation.

#### Provisions for post-trial care {30}

If serious changes occur during the study period, e.g., in relation to comorbid disorders requiring treatment, these are also followed up after the study period. Appropriate measures are taken for this purpose, such as outpatient or inpatient care or referral to other specialists.

Since there are hardly any specific measures for people with ASD, participants who were randomized initially to the treatment as usual group (TAU) are offered SCOTT&EVA or FASTER after the end of the study.

### Outcomes {12}

All outcomes will be assessed at baseline (T0), post-treatment (T1, 4 months after baseline), and follow-up (T2, 8 months after baseline).

The primary endpoint of our trial is the change of the total sum score from baseline (T0) to 4 months after baseline (T1) in social responsiveness as measured with the *Social Responsiveness Scale* (SRS-A adult, parent/spouse/other, [18, 19]).

The secondary outcome measures aim to differentially assess aspects of self-reported social responsiveness, social cognition, social skills, empathy, common comorbid psychopathology, self-esteem, life satisfaction, and quality of life. Almost all questionnaires and tests (see Table 1) are well-established, widely-used instruments with excellent psychometric properties (see also the “Data collection and management” section).

The measurement for social responsiveness (parent/spouse/other) at the follow-up measurement time point (T2) is also a secondary outcome.

**Table 1 Tab1:** Illustration of frequency of study visits, questionnaires, and tests

	SCR	T0	T1	T2
GAF (SCR: via telephone or personally)	x^1^	x^3^	x	x
Psychopharmacotherapy	x^1^	x	x	x
ADOS-2 (if lacking)	x^2^			
SCID-5-CV	x^2^			
CFT 20-R	x^2^			
MWT-B	x^2^			
Neo-FFI	x^2^			
AQ50	x^2^			
EQ40	x^2^			
WURS-K	x^2^			
ADHS-SB	x^2^			
TAS-26	x^2^			
Basis Documentation	x^2^			
SRS-A (patient)		x	x	x
SRS-A (parent/spouse/other)		x	x	x
SRS-A mod. (patient)			x	x
SRS-A mod. (parent/spouse/other)			x	x
MET (computer test)		x	x	x
BDI-II		x	x	x
SASKO		x	x	x
MSWS		x	x	x
FLZ^M^		x	x	x
WHOQoL-Bref		x	x	x
Freiburg Event List			x	x
Partnership Questionnaire (if appropriate)		x	x	x

*Abbreviations: GAF*, Global Assessment of Functioning (assessed by a telephone interview); *ADOS-2*, Autism Diagnostic Observation Scale; *SCID-5-CV*, Structured Clinical Interview for DSM 5, Disorders, Clinician Version; *BDI-II*, Beck Depression Inventory; *CFT 20-R*, Culture Fair Intelligence Test Revised; *MWTB*, Mehrfachwahl-Wortschatz-Intelligenz-Test; *AQ50*, Autism Spectrum Quotient with 50 items; *EQ40*, Cambridge Behaviour Scale with 40 items; *WURS-K*, Wender Utah Rating Scale, short form; *ADHS-SB*, Attention Deficit Hyperactivity Disorder, self-report; *TAS-26*, Toronto Alexithymia Scale; *SRS-A*, Social Responsiveness Scale (self-report, patient); *SRS-A (parent/spouse/other)*, Social Responsiveness Scale from parent or spouse, external assessment; *SRS-A mod. (patient; parents/spouse/other)*, modified version of SRS-A for measuring differences from baseline (T0) to post-treatment assessment (T1) and post-treatment assessment (T1) to follow-up (T2) in five gradations (considerably aggravated to considerably improved); *Neo-FFI*, Neo Five-Factor-Inventory; *MET*, Multifaceted Empathy Test; *FLZ*^*M*^, Life Satisfaction Questionnaire; *MSWS*, Multidimensional Self-worth Scale; *WHOQOL*, WHO Quality of Life; *SASKO*, questionnaire for social anxiety and social skills deficits; *Freiburg Event List*, questionnaire about life events; Partnership questionnaire for partner of the participant, if living in partnership and self-report; *SCR*, screening; assessment—*x1* first screening assessment (SCR I); *x2* second screening assessment (SCR II); *x3* have to be measured again if the last measurement was more than a month ago

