#### Intervention description {11a}

After the screening phase, eligible study participants will be included into the study and assessed at baseline (T0). Following baseline measurement of six participants, all six will be assigned to one of the three groups (FASTER, SCOTT&EVA, or TAU) via cluster randomization.

The Freiburg Asperger-Specific Therapy for adults (FASTER) intervention [2, 5, 13] has been developed, validated, and published in manualized form by the Freiburg Asperger Study group since 2004 as a specific group psychotherapy concept and offers a comprehensive approach for the treatment of adult patients with high-functioning ASD, implicating good language abilities and normal or above average IQ. Weekly 120-min group psychotherapy sessions will be held for 4 months for a maximum of six participants and two therapists in a closed group. Within this timeframe, participants will receive three different therapy modules in 16 group psychotherapy sessions altogether. At the beginning of the first basis module psychoeducation and information will be given about ASD as well as rules and aims of the group therapy. The module will continue with assessing individual strengths and weaknesses of the participants, as well as stress regulation management and knowledge about autism-related and individual demands (stimulus satiation, irritation, etc.), thereby offering adapted mindfulness techniques for autism, and autism-specific strategies for self-regulation. Information about alexithymia, in-depth comparison of autistic and sociotypical rules and strategies in social interaction, non-verbal and verbal communication, as well as perspective taking will be provided in the second module. Videotaped role plays of everyday life situations (like expressing gratefulness, needs, or criticism in different types of social contacts) with individualized feedback will be the core elements in the final advanced module.

Each single group psychotherapy session comprises three different parts. A short review of last week’s outstanding events or experiences of each participant will be shared with the group for the first 20 min of the session. If participants require clarification of urgent or important group-appropriate issues, they can receive feedback from other group members. This will be followed by a short mindfulness exercise that is especially adapted to individuals with ASD. Subsequently, the actual topic of the session will be introduced.

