### Participant timeline {13}

The measurement points are displayed in Table 2.

**Table 2 Tab2:** T_F/S_ (treatment) = FASTER: 16 sessions at 120 min, group psychotherapy, 1/week and a single treatment at beginning and end of treatment; SCOTT&EVA: 32-h computer training with a minimum of 2 h/week, this will be controlled by online tracking and supervised training at the beginning of week one and ongoing once per month; B_F/S_ = Booster sessions FASTER: 4 sessions at 120 min 1/month; SCOTT&EVA: 4 sessions at 30 min 1/month. Screening-visits –t_2_ and –t_1_, t0, t1, t2 are measurements for all groups FASTER, SCOTT&EVA, and TAU

	Study period							
	Enrolment		Allocation					
Visit No./timepoint	SCR I −t_**2**_	SCR II −t_**1**_	t0		FASTER or SCOTT&EVA	t1		t2
Procedure	Screening				Treatment phase		Follow-up phase	
**Month**	**−2**	**−1**	**0**	**Randomization**	**1–4**	**4**	**5–8**	**8**
**Inclusion/exclusion criteria 1**	●							
**Inclusion/exclusion criteria 2**		●						
**Written informed consent**		●						
**Baseline (T0)**			●					
**Interventions**					T_F/S_			
**Post-treatment measurement (T1)**						●		
**Booster Sessions for treatments**							B_F/S_	
**Follow-up measurement (T2)**								●
**AE/SAE**			●		●	●	●	●
**Psychopharmacotherapy**	●	●	●		●	●	●	●

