## Assignment of interventions: allocation

### Sequence generation {16a}

Subjects are randomized by cluster randomization in an allocation ratio of 1:1:1. The cluster size is set to 6 patients per cluster. This means that groups of 6 participants are built within each center, and these groups are randomly assigned to one of the three study arms. The randomization will not be stratified by center or other factors. An Internet-based randomization system (http://www.randomizer.at) will be used and the allocation sequence is created by computer-generated random numbers.

All transactions will be logged. The software’s GCP-compliance has been confirmed by the Austrian Federal Office for Safety in Health Care (BASG). Details of the randomization scheme will be specified in an external document accessible to the Institute of Medical Biometry and Informatics (IMBI, Heidelberg) only to minimize selection bias.

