## Assignment of interventions: blinding

### Who will be blinded {17a}

Randomization takes place after baseline. Study staff from each study center who measure post-treatment (T1) and follow-up (T2) are blinded regarding group assignment. Rater and therapy rooms are far apart, to support the blinding of the raters throughout the whole course of the study. Raters log at the measurement time points T1 and T2 for each study participant whether they are blinded or not. Due to study design and significantly different interventions in the study arms, therapists, study participants, and additional persons who are responsible for the external assessment for social responsiveness are not blinded. The biometrician and his representative will remain blinded until data base closure.

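### T1 is called post-treatment and is also set at 4 months after each patient's own baseline, but treatment cannot start before the cluster's sixth baseline; the two agree only if the six T0 visits nearly coincide

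*Protocol article*

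**What the plan says.** Four statements in the protocol article have to fit together.

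- **Endpoint timing.** Outcomes {12} gives the visits as "post-treatment (T1, 4 months after baseline), and follow-up (T2, 8 months after baseline" and the primary endpoint as the "change of the total sum score from baseline (T0) to 4 months after baseline (T1". The clock is the patient's own baseline, and T1 carries the label post-treatment.
- **Allocation.** Intervention description {11a}: "Following baseline measurement of six participants, all six will be assigned to one of the three groups". Sequence generation {16a} adds that "groups of 6 participants are built within each center", and Who will be blinded {17a} that "Randomization takes place after baseline".
- **Length of treatment.** Intervention description {11a}: "Weekly 120-min group psychotherapy sessions will be held for 4 months", in a closed group. The caption of Table 2 in Participant timeline {13} gives "16 sessions at 120 min, group psychotherapy, 1/week and a single treatment at beginning and end of treatment". SCOTT&EVA is planned as 32 hours of training over the first four months.
- **Schedule.** Table 2 puts t0 at month 0, randomization immediately after it, treatment in months 1–4 and t1 at month 4. It shows no time for a cluster to fill.

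The article does not limit the time between the first and sixth baseline of a cluster, and it does not count T1 from randomization or from the start of treatment.

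**The concern.** A patient whose baseline precedes the sixth has already used up part of the 4 months when treatment starts. If a site follows the stated clock, that patient's primary assessment can fall before treatment ends, earlier in the course the sooner the patient enrolled. If a site follows the label post-treatment, the interval from T0 to T1 exceeds the 4 months in the endpoint definition. Both sites could claim to follow the protocol while measuring different things.

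At stake is what the confirmatory comparison estimates. Under the stated clock it would be the effect of a treatment course that some patients have only partly received, probably biased toward no difference. An analysis plan cannot repair this later, because a questionnaire completed on the wrong date cannot be collected again.

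**Working it through.** **1. The plan's own figure.** Inputs from Sample size {14}: effect 0.4 for both comparisons, baseline correlation 0.2, design effects 1.25 (FASTER) and 1.05 (SCOTT&EVA, TAU), correlation of the test statistics 0.455, local two-sided level 0.026632.

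- Residual variance: 1 − 0.2² = 0.96.
- Mean of the SCOTT&EVA statistic at 87 per group: 0.4 / √(0.96 × (1.05 + 1.05) / 87) = 2.63.
- Mean of the FASTER statistic: 0.4 / √(0.96 × (1.05 + 1.25) / 87) = 2.51.
- Bivariate normal probability that at least one is significant: 0.801. The smallest n that reaches 0.80 is 87, as stated.
- Dropout: 87 / 0.75 = 116, rounded up to 120 (20 clusters of 6), so 360 in total.

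The sample size reproduces.

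**2. Slack in the schedule.** Sixteen weekly sessions span 15 weeks if the first falls on the randomization day, or 16 weeks if it falls a week later. That is 3.45 or 3.68 months (weeks × 7 × 12 / 365.25), without the single closing appointment. T1 falls before the end of treatment when wait + duration > 4 months. The tolerated wait is therefore 0.55 month (15 weeks), 0.32 month (16 weeks), or none if treatment takes the full 4 months.

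**3. Waits if T0 is taken on arrival.** This is an assumption: equal centers and even accrual. Each center enrolls 360 / 6 = 60 patients. Recruitment {15} gives 28 months of recruitment. Trial status has the last patient out at 28 months, which leaves 28 − 8 = 20 months. Both are used as a range. The k-th patient waits (6 − k) × (months / 60).

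| | 28 months | 20 months |
|---|---|---|
| Patients per center per month | 2.14 | 3.0 |
| Waits, patients 1 to 6 (months) | 2.33, 1.87, 1.40, 0.93, 0.47, 0 | 1.67, 1.33, 1.00, 0.67, 0.33, 0 |
| Mean wait (months) | 1.17 | 0.83 |
| T1 before end, 15 weeks | 4 of 6 | 4 of 6 |
| T1 before end, 16 weeks | 5 of 6 | 5 of 6 |
| T1 before end, 4 months | 5 of 6 | 5 of 6 |
| Mean share of treatment received by T1 (15 weeks, 16 weeks, 4 months) | 0.79, 0.76, 0.71 | 0.88, 0.85, 0.79 |

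With random (Poisson) arrivals and a 15- or 16-week course, the proportion with T1 too early is 64–72% (28 months) or 56–67% (20 months).

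**4. Waits if T0 visits are batched** (spread evenly over the window). Number of six with T1 before treatment ends:

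| Window | 15 weeks | 16 weeks | 4 months |
|---|---|---|---|
| Same day | 0 | 0 | 0 |
| 0.25 month | 0 | 0 | 5 |
| 0.5 month | 0 | 2 | 5 |
| 1 month | 3 | 4 | 5 |

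At 0.5 month and 16 weeks the two affected patients wait 0.5 and 0.4 month. With 4.35 weeks to a month, 3.5 × 4.35 = 15.2 and 3.6 × 4.35 = 15.7 weekly sessions fit before T1, so each misses one.

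**5. Illustration of the effect on power.** Repeating step 1 at 87 per group with the effect multiplied by 0.9, 0.8 or 0.75 gives power of 0.71, 0.61 or 0.55.

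**The case against.** The best defense is that T0 visits will be grouped. Table 2 puts randomization next to t0, and the allocation sentence fits six baselines scheduled together. Recruitment {15} says that centers keep waitlists and will search existing files, so batching is feasible. A journal article may also leave visit windows to the full protocol. This stands as far as the size goes: with T0 visits inside about two weeks the loss is small or nil. It does not remove the conflict. The article does not merely omit a window; it fixes the primary endpoint on a clock that, followed as written, can put T1 before the end of treatment. The treatment-policy strategy does not cover this either, since it addresses events such as withdrawal, not exposure cut short by the visit schedule.

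Three stronger readings are tempting, and the documents do not support them.

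- **A forecast of low power.** Power near 0.6 needs T0 on arrival, even accrual and benefit proportional to treatment received. The article states none of these. FASTER session counts also do not carry over directly to SCOTT&EVA, where 2 hours a week is a minimum and a participant can train faster.
- **The GAF rule as a precedent for ageing baselines.** The note to Table 1 says that GAF values "have to be measured again if the last measurement was more than a month ago". It is attached to the T0 entry and refreshes a screening value at T0. It says nothing about a T0 value that ages before randomization, and SRS-A is not measured at screening.
- **Follow-up that differs by arm.** One might infer that active arms would be timed by the end of treatment and TAU by baseline. Nothing says so: TAU patients also wait in clusters of six, and Table 2 gives one timetable for all groups.

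**Conclusion.** The timing statements are consistent only if a cluster's six T0 visits nearly coincide, and the article does not require that. The primary endpoint is therefore badly fixed, and the passages must be reconciled. The size depends on how sites schedule T0: from no patient affected (same-day baselines) to 4 or 5 of 6 (baselines on arrival, under the accrual assumptions above). The power figures show only what dilution would cost if it occurred. Type I error is not affected, since on the literal text all arms run on one clock from T0. The planned numbers of 87, 120 and 360 are correct for their inputs.

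**What to change.** Define T1 and T2 as 4 and 8 months after the cluster's randomization date, with the same clock and the same visit window in all three arms, and align the endpoint definition, the analysis section and Table 2 with it. The wait for the cluster to fill then no longer cuts into the treatment period before T1.

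Also keep the baseline recent, in one of two ways:

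- schedule the six T0 visits as a batch shortly before randomization; or
- set a maximum age for the informant SRS-A at randomization and repeat it if older.

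The cost is wording in the visit schedule, plus either some coordination of T0 visits or one repeat questionnaire for informants of early-enrolled patients. If neither safeguard is adopted, the T0–T1 interval for the first patient grows to about 4 + 1.67 = 5.7 or 4 + 2.33 = 6.3 months at the accrual rates above. The sample size calculation does not change, and nothing in the treatments has to change.

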#### Primary outcome

For social responsiveness, the *SRS-A* [19, 24] is used as an external assessment instrument that had to be completed in by caregivers, spouses, or other people who have sufficient insight into the respective participant’s social communication and interaction. The SRS-A is an internationally widely-used, well-established instrument with a patient and a caregiver/spouse version with very good sensitivity. The German adult version has been validated [18]. Due to psychometric properties and since it provides internationally comparable results, it is a good instrument to assess changes in social responsiveness as a consequence of therapy [24–27]. Good reliability and validity of the German adult version have been shown (Cronbach’s alpha .89) [24].

The SRS-A cut-off score for adults is 67 with a sensitivity of .85, and a specificity of .83 for autism spectrum disorder in comparison to patients with other mental disorders and typical developed individuals. There is no normed German version of SRS-A available so far, but a validation has already been published [24].

#### Secondary outcomes

Additional SRS-A measurements will be done for our secondary objectives.

The *Social Responsiveness Scale for adults*, second edition (SRS-A, 19), is also available in the form of a self-report. Compared to the SRS-1, the SRS-A has the additional variant for self-assessment and is eligible from 18 years onwards. The 65 items of the SRS-A are almost identical to the SRS-1 in terms of content, but in the SRS-A self-assessment, the statements are given in an ego perspective. The questionnaire comprises five subscales: social consciousness, social cognition, social communication, social motivation, and autistic mannerism. The Cronbach’s alpha for the total score is .89 for individuals within the autism spectrum.

As secondary outcome, we will assess changes in social responsiveness via the SRS-A self-report [24–26] for the global sum score as well as for each of the five subscales. With a modified answer version of the SRS-A, we will additionally ask about the specific difference between the beginning and the end of treatment with a five point Likert scale between “much worse,” “somewhat worse,” “stayed the same,” “somewhat better,” and “much better” instead of the original scale. The modified version is used for both the external evaluation and the self-report.

Furthermore, we apply the Global Assessment of Functioning (GAF), which is part of the Structured Clinical Interview for DSM-IV [17] and frequently used in clinical practice.

Social cognition is tested via the computer-based *Multifaceted Empathy Test* (MET, [28]), which is an instrument for measuring both cognitive and emotional empathy. The MET consists of 26 pictures of emotional scenes and participants are asked to rate the emotional state of the person shown in the picture out of four possible answers (cognitive empathy) and to rate how strongly they feel the emotion of the person in the picture using a 9-point Likert-scale (emotional empathy).

The MET is an objective photo-based test that has specifically been designed and validated in adults with ASD [28]. It allows the calculation of a performance score for correct mental state inference and a valid estimate of the level of emotional engagement/responsiveness towards others.

Comorbid disorders like depression and social anxiety are measured. Depression will be measured with the *Beck Depression Inventory*, second edition (BDI-II, [29]). It is a widely used questionnaire for depression (Cronbach’s alpha = .92). Social anxiety is measured with the *Questionnaire for Social Anxiety and Social Skills Deficits* (SASKO, [30]). It has five different subscales (anxiety for speaking and take center stage, anxiety for rejection, deficit in interaction, deficit in information processing, and loneliness). The first four dimensions build the anxiety deficit structure of the questionnaire. The sum score of these four dimensions with 40 items have good internal consistency (Cronbach’s alpha between .92 and .94 from four different studies) [30].

Self-worth is measured with the *Multidimensional Self-worth Scale* (MSWS, [31]). It has six subscales (emotional self-worth, social self-worth – safety in contact, social self-worth – handling of criticism, performance-related self-worth, self-worth in physical attractiveness, self-worth in sportiness), resulting in two higher-order dimensions (general self-worth, body related self-worth), and overall self-worth as total sum score. Internal consistency for the subscales is between .75 and .87, the higher-order dimensions between .85 and .92 and the overall score has a Cronbach’s Alpha of .93.

Life satisfaction is measured with the *Life Satisfaction Questionnaire* (FLZ, [32]). It consists of a general part and a part focusing on physical healthiness. In the study, the general part of the questionnaire is used with eight questions for different areas of life. All questions are answered in relation to importance and satisfaction. The scale about the importance of life areas has a Cronbach’s alpha of .82.

Quality of life is measured with the *Quality of Life Questionnaire from the WHO* (WHOQoL-BREF, [33]). It consists of four scales: physical and psychological health, social relationship, and environment. For the short version of the questionnaire used here, the internal consistency lies between .66 and .80 for the four scales, and between .83 and .84 for the total score.

Two other questionnaires have been constructed in Freiburg especially for adults with autism and are not validated until now. We use specifically formulated questions for potentially occurring life events and a partnership questionnaire where either partners or only one may be autistic. To date, no comparable questionnaires are available in Germany.

The *Freiburg Event List* (FEL) will be used to assess non-treatment life events and is included to evaluate possible moderation effects at post-treatment and follow-up.

